## Background

Cardiovascular disease (CVD) is still the leading cause of death in the world and the second cause of death in Western societies [1, 2]. Because of the ageing population, the prevalence and associated costs of CVD are expected to increase considerably [3]. Moreover, due to adverse lifestyle factors an increase in the prevalence of obesity and diabetes mellitus has been observed in the past 25 years. In addition, we are dealing with high levels of persistent smoking. These trends partly negate the beneficial effect of improvements in blood pressure and lipid control achieved in the last decades [4]. Therefore, prevention of (re)occurrence of CVD remains crucial.

To prevent CVD, national and international guidelines for cardiovascular risk management (CVRM) provide clinical and organisational recommendations [5–7]. However, implementation of evidence-based guidelines is far from optimal and treatment goals are often not achieved [8–10]. Thus, despite the availability of accurate guidelines, CVRM needs improvement.

In the Netherlands, integrated care programmes were introduced to implement CVRM in general practices in recent years. The integrated CVRM care programme includes a patient-centered focus, use of clinical information systems, execution by practice nurses (PNs) and systematic invitation of patients for a CV risk assessment. The integrated CVRM care programme is based on the Chronic Care Model (CCM) that focuses on informed and activated patients who interact with trained, proactive practice teams [11, 12].

Integrated programmes compose a promising procedure to enhance chronic care and management of cardiovascular risk factors. However, solid evidence on the effect of integrated care programmes for CVRM in primary care on outcomes such as blood pressure, cholesterol levels, smoking status and cardiovascular risk is limited [13–15].

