### The integrated CVRM programme

The intervention under study is the integrated care programme for CVRM (see Table 1), based on the Dutch CVRM guideline and the practical manual for CVRM provided by the Dutch Society of General Practitioners [7, 21]. The intervention includes features of the Chronic Care Model (CCM), such as self-management support (help patients to set limited goals and identify barriers to reach their goals), regular follow-up, registration of patient data in clinical information systems, a structured, nurse-led health care organization and easy accessible consultation of a specialist [22]. The aim of the integrated care programme for CVRM is to decrease the risk of CVD for patients with a high CV risk or history of CVD by lifestyle treatment and medication if needed. Treatment goals are according to the Dutch guideline for CVRM, including systolic blood pressure < 140/90 mmHg, LDL-cholesterol < 2,5 mmol/L, no smoking, BMI ≤ 25 kg/m2 (< 70 years) or ≤ 30 kg/m2 (≥ 70 years), > 5 days a week moderate intense physical activity > 30 min/day, and a healthy diet (daily 150–200 g vegetables and 200 g fruit; daily 30–40 g dietary fibers; twice a week 100–150 g fish, at least once fatty fish; maximum of 6 g salt per day; maximum of 2 (men) or 1 (women) alcohol consumptions per day).

**Table 1 Tab1:** Elements of the integrated care for CVRM

Element	Contents
Systematic selection of target population	Systematic screening of practice population based on ICPC-codes
	Systematic screening of practice population based on ATC-codes
	Check of medical records according to in- and exclusion criteria of the programme
Active invitation of patients for the programme	Active invitation for an intake consultation by letter
	Reminder in case of no response
Collaboration with different disciplines	Well trained practice nurses, supervised by GPs
	Optional involvement of physiotherapist or dietician
	Online consultation of medical specialist
Data registration in multidisciplinary information system for integrated care (KIS, Portavita®)	Including data on laboratory measurement, intake consultation and follow-up controls
Benchmark meetings	Comparison op patient data of general practice with national data
Laboratory measurement (prior to intake consultation)	Lipids (total cholesterol, HDL-cholesterol, TC/HDL-cholesterol ratio, LDL-cholesterol, triglycerides)
	Renal function (creatinine, GFR estimated by MDRD)
	Glucose
Intake consultation	

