### Usual care

Usual care is based on the Dutch CVRM guideline, describing how to calculate the CV risk and advice to lower this risk by lifestyle intervention and/or medication. However systematic identification of patients eligible for CVRM, actively inviting patients for a visit, regular follow-up and standardized collaboration with other disciplines in the health care chain are not routinely part of usual care. Usual care practices may work with a PN. Most PNs in the Netherlands have had a basic training in CVRM. Furthermore, data are not registered in an information system for integrated care and GPs do not participate in benchmark meetings.

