The endpoint visit consists of the same components as the intake consultation in the integrated programme for CVRM as described before. Data collected during the endpoint visit will be registered in the electronic medical record.

An up-to-date 10-years cardiovascular morbidity or mortality risk will be estimated according to the algorithm of the Dutch national guideline for CVRM. This algorithm is based on the SCORE-function, adapted to the Dutch population and converted from a mortality risk to morbidity and mortality risk (based on the MORGEN-cohort and the Rotterdam Study-cohort) [26–29]. The risk chart takes into account age, sex, smoking status, systolic blood pressure and total cholesterol-HDL cholesterol ratio [23, 24]. For patients taking blood pressure or lipid lowering drugs, the actual SBP and cholesterol levels during treatment are used. For patients with CVD the SMART-function will be used to calculate the CV risk [30]. This function is based on age, sex, smoking status, systolic blood pressure, history of diabetes mellitus, ischemic heart disease, cerebrovascular disease, aortic aneurysm, peripheral arterial disease, time since first diagnosis of CVD, HDL-cholesterol, total cholesterol, renal function (eGFR), and high-sensitivity CRP.

Furthermore, baseline data and data concerning health care use in the past year and in the period prior to the study will be collected by scrutinizing the electronic medical files.

Finally, GPs will be asked to complete a survey about the CVRM care, including questions on the practice setting (rural/urban, solo/group), organization of their practice, availability of trained PNs, CVRM programme and possibilities to refer for lifestyle treatment (social map).

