### Statistical analyses

The aim of the main analysis is to compare the SBP and LDL-cholesterol levels after 1 yr of follow-up between patients in the intervention group receiving integrated care for CVRM and the patients in the usual care group receiving usual CVRM care. For the main analysis we will use linear regression. For secondary outcomes, linear regression will be used for continuous outcomes, logistic regression for dichotomous outcomes and multinomial logistic regression for categorical outcomes. All analyses will be corrected for clustering.

Given that patients of clusters of patients are not randomly allocated to the intervention or usual care group, we anticipate that differences in baseline risk might be present between both groups. Hence, we will adjust the analyses for these confounders, including patient characteristics and practice characteristics. To do such adjusted analysis we a priori define the following baseline covariates which are well-known to be related to the outcomes: i) patient characteristics, including relevant medication use, such as blood pressure lowering drugs [32], anticoagulants [33] and lipid lowering drugs [34], relevant comorbidity, including COPD [35], heart failure [36, 37], atrial fibrillation [38], renal failure [39], ii) practice characteristics, such as involved disciplines in CVRM care (including number of PNs) [31], number of patients, and number of GPs. Results will be reported both without (i.e. crude results) and after correction for confounders. Confounders are defined a priori and not selected based on statistical significance.

Furthermore, we will examine whether the effect of the integrated care for CVRM is modified by differences in the following practice characteristics: practice organization (solo/duo/group), availability of CVRM protocol and existence of other disease management programmes (COPD, DM). This will be done by adding interaction effects.

All analyses are applicable to patient data matched on age and gender.

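### The adjusted model treats involved disciplines and practice-nurse numbers as baseline confounders, but baseline falls after programme adoption, so adjustment can remove part of the programme's effect

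*Protocol article*

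**What the plan says.** **The adjustment set.** Statistical analyses says "we a priori define the following baseline covariates which are well-known to be related to the outcomes". It then lists patient characteristics and "practice characteristics, such as involved disciplines in CVRM care (including number of PNs", followed by the numbers of patients and GPs. Reporting is fixed too: "Results will be reported both without (i.e. crude results) and after correction for confounders".

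**The programme.** The Background describes it as including "execution by practice nurses (PNs) and systematic invitation of patients for a CV risk assessment". Table 1 has an element on collaboration between disciplines, and the first content listed there is "Well trained practice nurses, supervised by GPs". The same collaboration is one of the five organisation strategies in the section of that name.

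**The comparator.** The Usual care section says that "standardized collaboration with other disciplines in the health care chain are not routinely part of usual care". It also says that "Usual care practices may work with a PN".

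**Timing and source.** Under Setting, practices could join from January 2016, and 37 of the 56 chose to do so before the study. Intake invitations went out from September to December 2016 (Recruitment, Intervention group). Study procedures sets t = 0 at the intake consultation. The practice-level source that the article describes is this: "GPs will be asked to complete a survey about the CVRM care, including questions on the practice setting". The survey's topics include the availability of trained practice nurses (PNs). No reference period is given.

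**The concern.** A confounder has to precede the exposure or at least be unaffected by it. Here one named covariate overlaps with the content of the exposure, and the time at which it counts as baseline falls after the practice took up that exposure. If the recorded value reflects the programme, the adjusted coefficient answers a different question: what the programme does beyond the disciplines and staffing it brings. The stated aim concerns the programme as a whole.

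The adjusted estimate matters most here. Practices chose their own arm, and the Limitations section relies on matching and multivariable analysis to deal with confounding. If the adjusted effect on systolic blood pressure (SBP) or LDL-cholesterol came out smaller than the crude one, a reader could not tell whether confounding or part of the programme's effect had been removed.

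**Working it through.** The plan gives no figure on this point to reproduce. The check sets the passages in order and then illustrates what follows from them.

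**Step 1: is the covariate part of the exposure?**

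- *Involved disciplines*: yes, in substance. Collaboration between disciplines is a Table 1 element and an organisation strategy, and its standardized form is described as not routine in usual care.
- *Number of PNs*: not as such. The programme calls for trained nurses and nurse-led delivery but sets no headcount, and usual care practices may have a PN.

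**Step 2: does the word baseline place the value before the exposure?** The order of events is:

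1. Practice-level entry is possible from January 2016, at three-monthly intervals.
2. Before intake, implementing practices organise themselves and their PNs identify patients and review records.
3. Patients are invited for intake from September to December 2016, and the intake consultation is t = 0.
4. The endpoint visit follows one year later.

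A value taken exactly at t = 0 therefore describes an intervention practice that is already running the programme. Only a value dated before step 1, or before that practice's own adoption, is sure to be free of it. The article does not tie the covariate to such a date.

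**Step 3: what would adjustment do?** Inputs from the Sample size calculation: effect 5 mmHg, intra-cluster correlation 0.05, 370 patients per group, 17 and 9 practices. Assumptions, not in the article: outcome SD 18 mmHg; a practice-level covariate M that the programme shifts by 0.5, 1 or 2 of its SDs; and a share s of the effect carried through M.

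The adjusted coefficient then targets the part not carried by M:

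adjusted effect = −5 × (1 − s)

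A practice-level simulation (4,000 runs per setting, ranges over the three shifts) agrees:

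| Share s (assumed) | Formula (mmHg) | Crude, simulated mean | Adjusted, simulated mean |
|---|---|---|---|
| 0% | −5.0 | −4.98 to −5.02 | −4.98 to −5.04 |
| 10% | −4.5 | −4.95 to −5.01 | −4.43 to −4.54 |
| 25% | −3.75 | −4.96 to −5.02 | −3.72 to −3.86 |
| 50% | −2.5 | −4.95 to −5.03 | −2.43 to −2.49 |

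The same proportions apply to the 0.3 mmol/L LDL-cholesterol difference: 0.3 × (1 − s) = 0.27, 0.225 and 0.15 for s = 10%, 25% and 50%. The simulation contains no confounding, so its crude column shows only what adjustment takes away. It does not show that the crude result would be right in this study.

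**Step 4: precision.** With s = 0 the SD of the crude estimate is about 2.1 mmHg:

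- patients per practice: 370/17 = 21.8 and 370/9 = 41.1
- between-practice variance: 0.05 × 18² = 16.2
- within-practice variance: 0.95 × 18² = 307.8
- √[(16.2 + 307.8/21.8)/17 + (16.2 + 307.8/41.1)/9] ≈ 2.10

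The simulated SD of the adjusted estimate is 2.2, 2.5 and 3.1 for shifts of 0.5, 1 and 2 SDs. The loss is not universal. With s = 50% and a shift of 0.5 SD, the crude SD is 2.97 and the adjusted SD 2.27, because M then also explains differences between practices.

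**The case against.** The strongest reply is that the plan calls these covariates baseline and fixes them in advance, and that staffing is a plausible true confounder. Adoption was voluntary, so a practice with more nurse capacity may have been both likelier to join and better at controlling risk factors. The Limitations section itself names supportive staff among the practice differences that could matter. Dietician and physiotherapist involvement is optional in Table 1. Usual care practices may have PNs, and the Strengths section expects similar referral opportunities in both groups. The survey's reference period is not stated and may be set out in a fuller document. Crude results are reported too, so any attenuation would be visible.

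Much of this stands. A reader might infer that PN headcount is itself part of the intervention, or that the covariate is nearly collinear with arm. The article supports neither: it sets no headcount and gives no figure relating staffing to arm. Nor does it support dropping staffing from the adjustment altogether, which would risk leaving real confounding in place.

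Two parts of the reply fail. The baseline label does not secure a pre-programme value when t = 0 follows adoption. And crude results reveal attenuation without showing its cause.

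**Conclusion.** The concern holds as a conditional one, and most clearly for involved disciplines. The plan adjusts for a variable that overlaps with a programme element, at a time that does not guarantee a value from before the programme, so the adjusted estimate can lose part of the effect of interest.

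A reader might go further and conclude that the adjusted estimate is certain to remove part of the effect. The documents do not support that. It is true only if the recorded values were changed by the programme, and the article does not date them. The loss is zero if the programme leaves the covariate unaltered. Under the assumed shares of 10% to 50%, a 5 mmHg effect would appear as about 4.5 down to 2.5 mmHg. The shares, the shifts and the SD of 18 mmHg are all assumptions, and the SD plays no part in the average attenuation.

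**What to change.** In the main adjusted model:

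- Define the discipline and PN-staffing covariates as each practice's values before roll-out: before January 2016, or before the practice's adoption date. The calendar date has the advantage of being defined for usual care practices as well.
- Obtain these values through the GP survey that is already planned.
- Keep practice size (numbers of patients and GPs).
- Leave disciplines and staffing during the programme out of this model. Show them only in an exploratory mediation or sensitivity analysis that is labelled as such.

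The cost is a change of wording in the analysis plan and at most one extra survey question. The downside is that earlier staffing has to be recalled in retrospect, and where it cannot be obtained some practice differences remain unadjusted. The change should be made before the outcome data are analysed.

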## Discussion

Disease management programmes for CVRM are gradually implemented in Western countries. So far it is unclear whether such integrated programmes have a positive effect on cardiovascular risk factors and this may lead to discussions between GPs, health insurers and policy makers. Previous studies are heterogeneous in studied interventions and study populations differ substantially in for example included risk categories and the way they are selected, e.g. by active screening or not. Also, adequate comparisons with control groups are lacking [20].

In the region of Zwolle, we have the opportunity to compare integrated care for CVRM with usual care. The aim of the ZWOT-CASE study is to evaluate the effectiveness of integrated care for CVRM compared to usual care in real practice. Since this is a pragmatic study, some choices in the study design were made that may have some methodological drawbacks. Below the major strengths and limitations of our study will be discussed.

### Strengths

First, the pragmatic design of the ZWOT-CASE study will give insight into whether integrated care for CVRM compared to usual care is effective in a real world environment. If integrated care for CVRM has a positive effect on our outcomes, it supports the idea that the intervention is beneficial in daily practice.

Furthermore, all the general practices are affiliated to the care group ‘Medrie’. The regional implementation of integrated care for CVRM will lead to a more uniform intervention and to less differences between general practices in the intervention group and consequently to less between-cluster variability. Also, the care group reached an agreement on integrated care for CVRM with the health care insurance for the coming 3 yrs, ensuring an adequately financed and stable health care environment during the follow-up of the ZWOT-CASE study. GPs in the usual care group are also members of the care group. This makes the usual care group probably more comparable with the intervention group with regard to socioeconomic characteristics and available opportunities for referrals.

Finally, a strength of the ZWOT-CASE study is the lenient inclusion criteria, i.e. patients with a CV risk of > 10%. Since usually more strict inclusion criteria are used in other regions, subgroup analysis will enable us to translate our results to other regions.

### Limitations

One limitation is the lack of random allocation to the two arms. This might lead to differences in practice characteristics between the intervention group and the usual group, and lead to either an over- or underestimation of the effect of integrated care for CVRM, when these differences are not adequately adjusted for. Besides, there may be differences in given care before implementation of integrated care for CVRM between different practices within the intervention group. This could also influence the effect of integrated care of CVRM. However, due to the complete registration of patient data in the Dutch general practice information system, we will be able to accurately collect patient data on years prior to the study and take into account the given care prior to the intervention. Furthermore, ample measures have been taken (notably matching of patients, multivariable analyses) to prevent confounding in our study.

Since patients will be selected from different general practices, we have to deal with a cluster effect. The intervention under study may be heterogeneous [40]. For example, differences in practice size, practice facilities and space, training of GP and staff, availability of supportive staff, time-management, attitude towards prevention and the GP-patient relationship might lead to cluster-level differences.

Another limitation of our study design is that it is not possible to blind GPs, PNs and participants for the intervention. Blinding is impossible due to the nature of the intervention. To minimize bias and maximize the validity of the results, participants are selected just before the end of the study. Also, during follow-up the general practices are not informed about which patients are identified as eligible to participate in the study.

A disadvantage of the regional approach of our study is the risk of contamination between the usual care group and the intervention group. Usual care may change in the direction of the intervention and therefore the effect of the intervention may be underestimated. However, as GPs in the usual care group do not use the guideline for the implementation of integrated care for CVRM, do not register patient data in an information system for integrated care, and yearly benchmark meetings are not mandatory, we expect the effect of contamination to be minimal. We will collect data on provided CVRM care to assess contamination.

The regional approach of this study could reduce the generalizability of the findings to other regions in the Netherlands. However, we expect that most of the integrated care programmes for CVRM are based on the same Dutch guideline for CVRM and the same international guidelines for CVRM.

The follow-up of 1 year could be too short to analyse the full effect of integrated care for CVRM. However, we expect that the largest gained improvements in cardiovascular risk factors will occur within 1 yr. Therefore, a follow-up of 1 yr will be sufficient to assess the effectiveness of the intervention on these cardiovascular risk factors. But, if integrated care for CVRM is effective, it would be interesting to analyse whether the effect continues. Also, improvements in cardiovascular risk factors will only translate in a lower cardiovascular morbidity and mortality in the longer term [3]. To observe the durability of an effect, and to assess the effect of integrated care for CVRM on absolute cardiovascular morbidity and mortality, studies with a longer follow-up period should be conducted.

Finally, a general limitation of studies in general practice is that due to a lot of variation in the organization of primary care across Europe and beyond [41, 42], the results of a study in one country will probably only be generalizable to countries with similarly organised primary health care systems. However, to support the implementation as well as continuation of disease management programmes scientific evidence is needed. Integrated programmes for CVRM have been introduced in Western countries in recent years. Evidence on the effect of such integrated CVRM care is very limited. The ZWOT-CASE study will give insight into the effectiveness of integrated care for CVRM compared to usual care in general practice.

